## Abstract

**Background:**

Although medical interventions play an important role in preserving lives and maternal comfort they have become increasingly routine in normal childbirth. This may increase the risk of associated complications and a less satisfactory birth experience. Antenatal hypnosis is associated with a reduced need for pharmacological interventions during childbirth. This trial seeks to determine the efficacy or otherwise of antenatal group hypnosis preparation for childbirth in late pregnancy.

**Methods/design:**

A single centre, randomised controlled trial using a 3 arm parallel group design in the largest tertiary maternity unit in South Australia. Group 1 participants receive antenatal hypnosis training in preparation for childbirth administered by a qualified hypnotherapist with the use of an audio compact disc on hypnosis for re-enforcement; Group 2 consists of antenatal hypnosis training in preparation for childbirth using an audio compact disc on hypnosis administered by a nurse with no training in hypnotherapy; Group 3 participants continue with their usual preparation for childbirth with no additional intervention. Women > 34 and < 39 weeks gestation, planning a vaginal birth, not in active labour, with a singleton, viable fetus of vertex presentation, are eligible to participate. Allocation concealment is achieved using telephone randomisation. Participants assigned to hypnosis groups commence hypnosis training as near as possible to 37 weeks gestation. Treatment allocations are concealed from treating obstetricians, anaesthetists, midwives and those personnel collecting and analysing data. Our sample size of 135 women/group gives the study 80% power to detect a clinically relevant fall of 20% in the number of women requiring pharmacological analgesia – the primary endpoint. We estimate that approximately 5–10% of women will deliver prior to receiving their allocated intervention. We plan to recruit 150 women/group and perform sequential interim analyses when 150 and 300 participants have been recruited. All participant data will be analysed, by a researcher blinded to treatment allocation, according to the "Intention to treat" principle with comprehensive pre-planned cost- benefit and subgroup analyses.

**Discussion:**

If effective, hypnosis would be a simple, inexpensive way to improve the childbirth experience, reduce complications associated with pharmacological interventions, yield cost savings in maternity care, and this trial will provide evidence to guide clinical practice.

## Background

Pain during labour and childbirth represents a complex interaction of multiple physiological and psychological factors [1]. Techniques such as epidural analgesia, have been shown to be the most effective form of pain relief in labour[2] but, can deprive the mother of an optimal birth experience[3] and are associated with adverse effects such as post-dural puncture headache and neurological injury [4,5]. Although, long term sequelae are rare, such complications can be debilitating and extremely distressing when they occur [6]. All pharmacological interventions cross the placenta to some degree which leads to concerns of adverse effects on the fetus. The recent Australia and New Zealand College of Anaesthetists (ANZCA) working party report emphasises that non-pharmacological treatment options should be considered before analgesic medications are used particularly just before delivery [1]. Women's desires for and expectations of pain relief during labour and delivery vary widely [7] and high quality pain relief does not necessarily equate with a high level of satisfaction [8]. The increasing medicalisation of childbirth [9] has led many women to look for alternative means of relieving labour pain [10].

Fear, anxiety and maternal feelings of a loss of control frequently play a role in the incidence and intensity of pain during childbirth and are associated with an increased risk of post-traumatic stress disorder[11] and postnatal depression [12,13]. Hypnosis is a psychological intervention that has been shown to provide analgesia and reduce anxiety and in the peri-operative setting [14-16] and since the mid 1980s has been advocated as a useful tool in the management of depression [17,18]. Claims that hypnosis is a safe and valuable tool in pregnancy and childbirth [19-21] is supported by numerous reports in the literature describing the successful use of hypnosis as an analgesia adjunct during childbirth. [22-24] For many years hypnosis has suffered greatly from misunderstanding and prejudice [25]. However, more recently the use of clinical hypnosis has become an area of increasing clinical interest and research [26-28] Advances in neuro-imaging have led to an understanding of the neuro-physiological changes occurring during hypnosis induced analgesia [29]. The anterior cingulate gyrus has been repeatedly demonstrated, by positron emission tomography, to be one of the sites in the brain affected by hypnotic modulation of pain. [29-31] The suppression of neural activity, between the sensory cortex and the amygdala – limbic system, appears to inhibit the emotional interpretation of sensations being experienced as pain. Hypnosis appears to be a state of narrow focused attention, reduced awareness of external stimuli, and an increased response to suggestions [32,33]. Suggestions are verbal or non-verbal communications that result in apparent spontaneous changes in perception or behaviour. These therapeutic communications are directed to the patient's subconscious and the responses are independent of any conscious effort or reasoning [34]. Potentially, medical hypnosis could be used alone for pain relief as part of a woman's care during childbirth. In practice however, hypnosis is best seen as an adjunct to facilitate and enhance other analgesics. The well recognised problems associated with current analgesia techniques and the increasing medicalisation of childbirth has led many women to look for an alternative means of relieving pain in labour [10]. Bonica estimates that up to 25% of women obtain complete analgesia when using hypnosis for pain relief in labour [35]. The responsiveness of women to hypnosis appears to be increased in pregnancy and in primiparous when compared with multiparous women [36,37]. A wide variety of personnel have used hypnosis effectively including medical students, [38] psychologists, [39,40] hypnotherapists[37] and obstetricians [41,42].

Systematic review evidence suggests that learning hypnosis techniques for use in childbirth would allow mothers to reduce their need for pharmacological analgesia, and other interventions such as intravenous oxytocics, and increase their chance of having a spontaneous vaginal birth[10,22,43]. Until recently, evidence of the effectiveness of hypnosis as an analgesia adjunct during childbirth was limited to three small trials being of adequate quality for meta-analysis. In addition the maternal populations under investigation did not have access to an "on demand" epidural service for labour analgesia which is widely available in many developed countries. A recent large study from the USA investigating the preparation of women for childbirth using hypnosis in the 1st trimester[44] will soon be available for inclusion in an updated meta-analysis. Neither the intervention nor the number of sessions were standardised in this study which was performed over a ten year period in the USA. Such features of previous studies limit the reproducibility of the intervention and decrease external validity.

Since April 2002, we have been developing an antenatal hypnosis training program for women in late pregnancy (after 35 weeks gestation) to be utilised for anxiolysis and as an analgesia adjunct during childbirth. Initially, we were seeing women on an individual basis. However increasing demand for hypnosis preparation for childbirth from mothers, midwives and obstetricians at our institution has led us to our current practice of training groups of 5–10 women/week in self hypnosis techniques developed along the lines described by Waxman, [45]. McCarthy [21,46] and Bjenke [24]. The hypnosis training program has continued to develop over the last three years utilising advice from senior clinical hypnotherapists in Australia and New Zealand with expertise and substantial experience of preparing over 1000 women in hypnosis preparation for childbirth. The intervention lasts approximately one hour and the hypnosis sessions are held for three consecutive weeks. Birth outcomes of 77 antenatal women taught hypnosis in preparation for childbirth between January 2003 and August 2004 were compared with parity matched controls delivering after 37 weeks gestation during 2003 at our institution. Primiparous women, receiving hypnosis preparation, used fewer epidurals than controls 18/50 (36%) vs 765/1436 (53%) (RR0.68, 95%CI 0.47,0.98) and less augmentation 9/50 (18%) vs 523/1436 (36%) (RR 0.48, 95%CI 0.27,0.90) [47]. These findings are consistent with those of our systematic review [22].

### Number of hypnosis sessions

Although most clinical hypnotherapists use three or more sessions antenatally when training women with hypnosis preparation for childbirth, Rock et al found hypnosis effective in untrained mothers during their labour [38]. Our clinical experience at our own institution suggests that the intervention is optimally delivered when three sessions are scheduled in late pregnancy. Interestingly, despite differences between trials in the timing and number of hypnosis interventions reported, outcomes are consistently in favour of hypnosis [22]. However, this could simply reflect possible publication bias.

### Timing of the intervention

Tiba suggests that as pregnancy progresses responsiveness to hypnosis and suggestion increases [36]. Our experience over the last three years has found that the vast majority of women have little difficulty learning this technique in the last four weeks of pregnancy.

### Groups vs individual administration of hypnosis

Leeb successfully used hypnosis in groups of up to 20 women in preparation for childbirth[48] while Harmon demonstrated a range of beneficial outcomes following antenatal hypnosis training in groups of 15 women [39]. Our own experience suggests that group hypnosis is effective and allows far more women to receive the intervention than would be the case with individual administrations. Some practitioners claim that an individualised approach is more effective but this has not been shown in a study of the effectiveness of hypnosis in treating hyperemesis [49].

#### Multiparous vs nulliparous

Previous randomised comparisons of hypnosis in this setting have investigated nulliparous women only. Two hypnosis studies investigating multiparous women used parity matched controls. These reports show similar (but reduced) treatment effects in favour of hypnosis [37,47].

#### Evidence of the effectiveness of hypnosis in the management and prevention of anxiety and postnatal depression

Hypnosis has recently becoming advocated as a useful non-pharmacological intervention in the treatment of depression [17,50]. There are several reports of a low incidence of postnatal depression associated with women preparing for childbirth using hypnosis techniques although comparative data is lacking [23,46] In addition, there is convincing evidence in the peri-operative setting that the use of hypnosis decreases patient anxiety and reduces overall costs [28,51,52].

#### Safety of hypnosis in childbirth

There are two published reports of a complication of hypnosis associated with an obstetric patient. One involved a parturient prior to labour exhibiting psychotic symptoms believing that she had been assaulted, [53] and the other involved a treatable post partum anxiety and compulsive behaviour associated with the use of hypnosis during labour [54]. Other reported problems with the use of (non obstetric) medical hypnosis in the literature have been mainly associated with the use of age regression techniques, by inexperienced practitioners, or in patients with psychoses [53]. It has been recommended that hypnosis should be used by practitioners within their field of expertise [55]. This is consistent with the view of a British Medical Association report confirming the relevance and appropriateness of the use of hypnosis by obstetricians and anaesthetists [56]. The mythology surrounding hypnosis that it is too time consuming, limits free will or induces amnesia of the birth experience are dispelled both by Werner[53] and more recently Nash [57]. There appears to be little basis for the fears surrounding these supposed dangers of hypnosis in obstetrics, although such opinions may have been a deterrent to its application [53].

### Supplementing hypnosis using an audio compact disc (cd) at home and in labour

Several workers ask patients to listen to an audio tape of hypnosis suggestions at home as practice in their preparation for childbirth re-enforcing the techniques learned in the classroom [39,46]. The heterogeneity seen in our systematic review[22] can be explained by the use of supplemental tapes of suggestions, in one of the studies, in addition to live preparation [39] This appears to support the view that it is beneficial for subjects to practice the intervention using taped suggestions at home [21]. There are however no randomised studies to confirm whether listening to hypnotic suggestions, on an audio tape or audio compact disc (cd), is of additional value. However the use of a tape or audio cd for re-enforcing the suggestions is a simple, cheap supplement to our hypnosis sessions that allows the intervention to be standardised and maximises external validity. The effectiveness of standardised over individualised suggestions during hypnosis has been studied previously [58]. If the audio cd is shown to be an effective intervention it could be easily implemented in other hospitals with no experience of hypnosis preparation for childbirth.

### Development of the structured intervention delivered by audio cd on hypnosis

Audio cds on hypnosis were developed in our institution following increasing requests from patients for a supplement to what was learned in the live hypnosis sessions. An experienced physician who has practiced full time hypnotherapy for over 10 years and whose practice involves regular hypnotherapy preparation for childbirth observed our hypnosis group sessions for several weeks and took notes of the types of suggestions utilised during each session. Our antenatal hypnosis training sessions are based on published scripts of suggestions, by experts in the administration of hypnosis in childbirth, combined with our own clinical experience. A final written script for each session based on our current clinical practice in training women using hypnosis in preparation for childbirth was agreed by the hypnotherapist members of our research team. These scripts were used to produce three audio cds that mirrored our current hypnosis preparation for childbirth training program. The audio cds were produced at a local recording studio and each lasted between 21 and 32 minutes. A 4th audio cd lasting 18 minutes has also been developed for use during labour and childbirth. Multiple copies were made through our institution's digital media department. The cds are labelled with a caution that they should not be used while operating machinery or driving. Two lead investigators' names ([name] and [name]) and contact phone numbers of our institution are shown on each cd label. Participants were advised that the cds are for their use alone as part of the HATCh trial.

Although there is evidence of the effectiveness of hypnosis for labour analgesia, too few women have been rigorously investigated in late pregnancy and trial heterogeneity prevents clear recommendations of what constitutes an effective intervention. Further adequately powered well-designed trials are required.

This trial seeks to determine the efficacy or otherwise of antenatal group hypnosis preparation for childbirth in late pregnancy.

### The specific aims of this study are to assess whether antenatal hypnosis preparation for childbirth:

1. is an effective way of reducing maternal use of pharmacological analgesia

2. reduces the incidence of adverse effects on the mother

3. reduces the incidence of adverse affects on the baby

4. impacts on the mother's emotional well being

5. is cost effective

### Additional specific aims

6. To compare two methods of delivering antenatal group hypnosis in a double blind fashion, one method using a hypnotherapist to deliver the intervention followed by an audio cd on hypnosis for re-enforcement of the techniques learned. The other method is to use the an audio cd on hypnosis alone administered by a nurse with no hypnotherapy training.

**[see **Additional file 1**] **for detailed hypotheses

## Methods/design

### Design of the study

A single centre, randomised controlled trial using a 3 arm parallel group design to assess the effects of hypnosis preparation for childbirth in late pregnancy as a means of reducing analgesia requirements in labour and improving other birth outcomes.

Group 1 participants receive antenatal hypnosis training in preparation for childbirth administered by a qualified hypnotherapist with the use of audio compact discs on hypnosis for re-enforcement; Group 2 consists of antenatal hypnosis training in preparation for childbirth using audio compact discs on hypnosis administered by a nurse with no training in hypnotherapy; Group 3 participants continue with their usual preparation for childbirth with no additional intervention.

The study setting is the largest tertiary maternity unit in South Australia. Participant inclusion criteria are women > 34 and < 39 weeks gestation, with a singleton, viable fetus, vertex presentation, who are not in active labour (active labour is defined as cervical effacement and dilatation associated with regular uterine contractions) and who are planning a vaginal birth. Exclusion Criteria are: previous hypnosis preparation for childbirth; poor understanding of English requiring a translator; women who are already enrolled in another pregnancy trial where analgesia requirements are an outcome measure; active psychological or psychiatric problems such as: active depression requiring treatment by a psychiatrist; schizophrenia; prior psychosis; severe intellectual disability. Women with pain caused by specific pathological entities such as: congenital neuromuscular disorders; spina bifida; metastatic disease; osteoporosis; rheumatoid arthritis; fractures, were also excluded.

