### Allocation concealment

We will be provided with the group allocation for each individual participant via telephone or a networked computer program. Allocation concealment is assured as the participant ID, parity and eligibility for trial entry is confirmed and recorded centrally prior to verifying a participant's group allocation. Participants assigned to hypnosis groups are to be given appointments by our research assistant to commence antenatal group hypnosis training as near as possible to 37 weeks gestation.

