### Treatment schedules

A researcher is responsible for base line data management, collection and co-ordinating appointments with the hypno-therapist and nurse supervising Group 1 and 2 participants respectively, directing women to their allocated interventions. Following baseline demographic data collection which includes the administration of the Edinburgh Postnatal Depression Scale (EPDS)[61], Spielberger[60] and Creative Imagination Scale (CIS)[62], trial participants are informed of where and when to attend their allocated sessions. The two interventions are administered in groups of up to ten women at our institution's group physiotherapy room. Participants allocated to an intervention are requested to attend sessions which are scheduled as near as possible to 37 weeks gestation and are held at weekly intervals for three consecutive weeks. Those women having a planned induction of labour will be allocated their hypnosis sessions as near as possible to commence within three weeks of the induction date rather than the original expected date of confinement (EDC).

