#### Power calculation

It is proposed that sufficient women be randomised to provide reliable evidence of the effects of antenatal hypnosis regarding the primary outcome measure of this study: the incidence of not using pharmacological pain relief during labour. An audit of 100 consecutive mothers birthing at the Women's and Children's Hospital in May 2004 showed an incidence of using one or more pharmacological interventions of 80%. In order to show a clinically relevant fall of 20% in the number of women requiring pharmacological analgesia ie from 80% to 64%. Using a 2 tailed calculation (Nquery advisor computer program V.5) a study with 80% power would require each group to contain 135 women to detect this difference at the 0.05 level.

Complete collection of the primary endpoint is likely as all analgesia techniques used such as Entonox, pethidine and epidural analgesia are documented routinely in the labour ward birth register and medical record by the woman's treating midwife. We plan to recruit 150 women/group as we estimate that 10% of participants' will deliver prior to receiving their allocated treatment. The findings of our case matched control study at the Women's and Children's Hospital[47] are consistent with those of our systematic review of the literature on this topic [22]. No comparative trials have investigated the effects of hypnosis on the incidence of postnatal depression although acknowledged experts in the field report a low incidence in women taught hypnosis (<1%) [21]. The prevalence of post-natal depression in several recent studies in Australia is between 13 and 18% [63]. Our proposed study has a power of 80% at the 0.05 level of significance to show a reduction from 16% to 5.4% for this secondary outcome. For normally distributed continuous measures (eg EPDS) we would be able to detect shifts of 0.4 SD with a power of 80 % between individual arms of the study (n = 135 per group). Comparisons which exploit the two treatment groups (assuming a conservative estimate of postnatal data in 270 subjects in Groups 1 and 2) would have 80% power to detect a shift of only 0.28 SD.

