#### Sub-group analyses

Subgroup analyses of primary outcomes will be performed for women regarding; induced vs spontaneous labour; attendance at all three sessions, whether each session cd was used at least once; size of group < 3 women, hypnotist, women's hypnotisability as measured by the CIS, women's beliefs; on whether they were in experimental group, women's beliefs of the efficacy of hypnosis prior to labour, Women's expectations of requiring an epidural, Women's expectations of having a normal spontaneous birth, Previous experience of non childbirth hypnosis or yoga. hypnotisability as measured by the Creative Imagination Scale. Some women will not attend the sessions to which they are allocated. We have tailored the hypnosis intervention so that most of the skills are learned in the first session and nearly all the skills are delivered by the second session. The third session is for re-enforcement and consolidation. Any women giving birth prior to completing all three sessions will be analysed both on an "intention-to-treat" basis and with total session exposure as a predictor.

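### Entry up to just under 39 weeks does not fit three weekly sessions meant to start near 37 weeks: most late entrants get a truncated programme, and a dropout inflation does not offset the resulting intention-to-treat dilution

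*Protocol article*

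**What the plan says.** Under Design of the study: "Participant inclusion criteria are women > 34 and < 39 weeks gestation". The abstract gives the same window. Under Allocation concealment, women in the hypnosis arms are to "commence antenatal group hypnosis training as near as possible to 37 weeks gestation". Under Treatment schedules, the sessions "are held at weekly intervals for three consecutive weeks". Women with a planned induction have their sessions re-timed to the induction date; nothing comparable is stated for women who enter late.

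On content, Sub-group analyses says that "most of the skills are learned in the first session and nearly all the skills are delivered by the second session", with the third session for consolidation. Births before the third session are to be analysed by intention to treat and also with the number of sessions received as a predictor.

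On sample size, Power calculation takes analgesia use of 80% against 64%, two-sided 0.05 and 80% power, which gives 135 per group. It raises this to 150 because "10% of participants' will deliver prior to receiving their allocated treatment". The abstract puts it as a range: "We estimate that approximately 5–10% of women will deliver prior to receiving their allocated intervention".

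**The concern.** The upper entry limit lies almost two weeks after the intended start, and the third session falls two weeks after the first. A woman who enters after 37 weeks cannot start on target, and one who enters close to 39 weeks would have to pass 40 weeks, and perhaps 41, to complete the programme.

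Women who give birth before or during the programme remain in their allocated arm under intention to treat. If they gain less, the expected difference from usual care shrinks. A null result would then be hard to read, because it could mean that hypnosis does not work or that it was not delivered in full. The session-exposure analysis does not resolve this. Exposure depends on when the woman gives birth, and controls have none, so it is not a randomised comparison.

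The one numerical safeguard, the step from 135 to 150, covers only births before any treatment. It also treats those women as if they left the analysis.

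**Working it through.** **1. Calendar.** Entry at 38w6d with a wait of 0 to 7 days for the next weekly group puts session 1 at 38w6d–39w6d, session 2 at 39w6d–40w6d and session 3 at 40w6d–41w6d.

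**2. Share giving birth before each session.** The documents give no distribution of gestation at entry or at birth, so these inputs are assumptions. Let gestation at birth be Normal(μ, σ), with all births by 42 weeks, conditional on being undelivered at entry e:

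P(birth before t) = [Φ((t−μ)/σ) − Φ((e−μ)/σ)] / [Φ((42−μ)/σ) − Φ((e−μ)/σ)]

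Example: μ = 39.6, σ = 1.3, e = 38.5. The denominator is 0.968 − 0.199 = 0.769.
- No wait: session 2 at 39.5 gives (0.469 − 0.199)/0.769 = 0.35; session 3 at 40.5 gives (0.756 − 0.199)/0.769 = 0.72.
- Half-week wait: session 1 at 39.0 gives (0.322 − 0.199)/0.769 = 0.16; session 2 at 40.0 gives (0.621 − 0.199)/0.769 = 0.55; session 3 at 41.0 gives (0.859 − 0.199)/0.769 = 0.86.

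The next figures average over entry at 38–39 weeks, with either no wait or a wait uniform on 0–1 week, for (μ, σ) = (39.3, 1.6), (39.6, 1.3) and (40.0, 1.2):
- no session: 0–18%
- fewer than two sessions: 28–55%
- fewer than three sessions: 65–85%

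Capping late births at 42 weeks instead of truncating there gives 0–17%, 26–52% and 62–81%. Other pairings within the same ranges of mean and SD widen the last figure, but it stays above one half in every case checked.

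**3. The plan's sample size.** With p₁ = 0.80, p₂ = 0.64 and mean 0.72:

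n = [1.96√(2×0.72×0.28) + 0.8416√(0.16 + 0.2304)]² / 0.16² = 1.770² / 0.0256 = 122.4

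With continuity correction: (122.4/4) × [1 + √(1 + 4/(122.4×0.16))]² = 134.6, so 135. Then 135/0.9 = 150. Both figures reproduce exactly, so the plan used the continuity-corrected formula.

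**4. The same 10% as dilution.** If a fraction d of a hypnosis arm receives nothing but stays in the analysis, the arm's rate is 0.64 + 0.16d. At d = 0.10 this is 0.656, a difference of 14.4 points instead of 16. Continuity-corrected power at 150 per group:

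Φ{[0.144 − 1/150 − 1.96√(2×0.728×0.272/150)] / √((0.16 + 0.656×0.344)/150)} = Φ(0.0366/0.0507) = Φ(0.722) = 76.5%

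| d | corrected | uncorrected |
|---|---|---|
| 0 | 84.5% | 87.4% |
| 5% | 80.7% | 84.1% |
| 10% | 76.5% | 80.3% |
| 20% | 66.6% | 71.3% |
| 30% | 55.2% | 60.4% |

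On the plan's own formula, d = 10% needs 163 per group, not 150.

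**5. What late entry adds overall.** Assume entry uniform from 34.2 to 39 weeks, which makes 38-week entrants about one fifth of recruits (an assumption), and a wait of up to a week. About 6–9% of all recruits then get no session. Excluding the 38-week entrants would raise the expected difference by about 0.3–0.4 points if one session suffices, and by about 0.9–1.2 points if two are needed.

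**The case against.** The start at 37 weeks is a flexible target, so entering later breaks no rule. The programme was deliberately front-loaded, with most skills in session 1. CDs of missed sessions can be posted (Compliance with treatment schedules), and in Group 2 the CDs are most of the intervention. The protocol foresees early births, and its 5–10% agrees with the modelled 6–9% receiving no session. Recruiting women who present late is a legitimate pragmatic choice, and intention to treat then estimates the effect of offering the programme.

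Much of this stands. The allowance for untreated women is plausible in size. The intention-to-treat estimate is valid for the offer, and removing late entrants alone would change the expected difference little.

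Three things do not fall away. A posted CD is no help to a woman who has already given birth. Calling session 3 consolidation sits uneasily with Group 1's schedule, which places the pain control techniques and the lower-body anaesthesia imagery there, while the primary outcome is analgesia use. And a correctly sized 10% is still handled as the wrong kind of loss.

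A reader might infer that the trial does not test hypnosis in late entrants, or that they are nearly untreated. The documents do not support this. At least four in five of them get a session under the working assumptions, and the protocol puts most of the content there. A reader might also conclude that the effect in them halves. With 51% receiving fewer than two sessions, 16 × 0.49 is about 8 points, but only if one session has no effect at all, which contradicts the protocol's account. If one session suffices and 16% get none, the figure is 16 × 0.84 = 13.4 points.

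**Conclusion.** The point holds as a mismatch between entry window and programme, and as a flaw in how the sample size allows for it. That women entering close to 39 weeks reach session 3 only around 41 weeks is calendar arithmetic. That most women entering from 38 weeks miss session 3 (about 65–85%) rests on assumed birth distributions, though it is a majority in every case checked. Fewer than two sessions (28–55%) depends heavily on the wait for a group, and no session at all (0–18%) is a minority outcome.

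The power point does not depend on those assumptions. At the protocol's own 10%, 150 per group gives about 76.5% on the formula that produced 135, and 80% without continuity correction. At 5% the target is met either way. Births part-way through the programme come on top and are not allowed for. Their cost cannot be fixed from the documents, because neither the share of late entrants nor the effect of a partial programme is given.

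**What to change.** - **Timing of randomisation.** Keep consent and baseline measures from 34 weeks. Make the existing telephone randomisation call as close as possible to the first scheduled session, ideally on the day or the day before, after reconfirming that the woman is undelivered, that presentation is vertex and that she still plans a vaginal birth. This removes pre-treatment births from all three arms alike, before allocation. If 150 per group are still randomised, corrected power rises from 76.5% to 84.5% when 10% would otherwise have been untreated. If 450 women consent and 10% deliver first, 405 are randomised, 135 per group, and power is 80.1%, as the plan intends. A call made a week ahead gains little.
- **Entry limit and schedule.** Reconcile the upper limit (abstract, Design of the study) with the stated start and length of the programme (Allocation concealment, Treatment schedules). One way is to close randomisation to women who can no longer start near the intended time, leaving the session schedule as it is. This is the more debatable part, since it gives up recruitment and breadth for fuller exposure.
- **Power statement.** Use one figure for pre-treatment births, since the abstract says 5–10% and Power calculation 10%. Count those that remain as dilution under intention to treat, and show power over a range for partial delivery.

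The cost is one extra short contact before allocation, some consented women lost before randomisation (about 450/0.9 = 500 consents to randomise 450 at 10%), and fewer late-presenting women if the limit is lowered.
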